## Evaluation of Suspected Tumor Recurrence

If local recurrence or progression is detected or suspected on follow-up MRIs in the region of prior GK, routine work-up with serial MRI, DSC-PMR, or PET scans may be done at the discretion of the treating physician. Surgical resection or biopsy for confirmation should be considered if clinically feasible; however, this is not mandated by the protocol and will be at the discretion of the treating physician.

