## Data Management

Clinical MR images will be sent to the Clinical Desktop system and will have standard clinical interpretations provided by the Department of Radiology. The investigational MRI imaging at Week 1 after GK will be reviewed by [name] (co-principal investigator) and reported in the Clinical Desktop system. This represents potential benefit to the patients, as incidental findings of new brain metastases, intracranial bleeding, or stroke may be detected early. For clinical sequences, post-processing will be performed according to standard protocols. In addition, research and clinical MR data without identifying patient information will be archived on the Central Neuroimaging Data Archive (CNDA) to allow for long-term follow up.

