## Processing of DSC-PMR

All MRI data will undergo coregistration and will be resampled into atlas space for viewing and processing. DSC-PMR will be processed to obtain rCBV, rCBF, rPH, PSR for each region of interest (22), see Appendix C. Regions of interest (ROI) will be generated based upon the clinical T1-post contrast and FLAIR images. ROI will include the enhancing tumor volume, the non-enhancing area of T2 hyperintensity surrounding the enhancing tumor, and a matching ROI from normal brain in the contralateral hemisphere. Given the DSC-PMR data will not be used in clinical care, the parameters in Appendix C may be completed in batch up to 6 months from the completion of radiosurgery.

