## Definition of Clinical Outcomes

Local tumor recurrence versus radiation necrosis can be a difficult diagnostic dilemma. The gold standard for this diagnosis will be based upon pathological diagnosis, when available. We would recommend any suspicious lesion be investigated and biopsied. If biopsy is not possible, the patient will be followed clinically and radiographically. Cases where clinical and radiographic findings demonstrate progressive disease, as defined by the MacDonald criteria (20), will be considered as recurrent tumor. Radiation necrosis will be defined by pathology, when available. When no pathology is available, we will use the final clinical diagnosis based on clinical course and management. Complete response is defined as no residue enhancing lesion on MRI. Elsewhere brain failure is defined as appearance of brain metastases outside of prior GK region, which can be diagnosed radiographically and does not require pathological confirmation. Clinical deterioration will be assessed based on the KPS scale (Appendix A).

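### DSC-PMR may help decide whether an unbiopsied lesion counts as local recurrence, so the label used to judge Week 1 DSC-PMR is not kept independent of it, and its apparent accuracy may be biased upward

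*Protocol*

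**What the plan says.** **Predictor.** Section 2.1 makes the change in DSC-PMR parameters from baseline to Week 1 the predictor of time to local progression. Section 10.4 also analyses absolute post-treatment values, and measures accuracy by ROC curve and AUC against local recurrence.

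**Work-up.** Under section 5.6, once recurrence is detected or suspected on follow-up MRI, "routine work-up with serial MRI, DSC-PMR, or PET scans may be done at the discretion of the treating physician". Biopsy or resection is to be considered, but "this is not mandated by the protocol and will be at the discretion of the treating physician".

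**Label.** Section 10.3 starts from pathology: "The gold standard for this diagnosis will be based upon pathological diagnosis, when available". Without biopsy, the recurrence rule is: "Cases where clinical and radiographic findings demonstrate progressive disease, as defined by the MacDonald criteria (20), will be considered as recurrent tumor". The necrosis rule is: "When no pathology is available, we will use the final clinical diagnosis based on clinical course and management". Neither rule says which imaging may or may not count.

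**Recording.** Footnote A of the study calendar has the coordinator take outcomes from the routine medical record. Appendix B asks only for an X per lesion under complete response, local failure or radiation necrosis.

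**Clinical use.** The Week 1 investigational scan is read by a co-principal investigator and "reported in the Clinical Desktop system" (section 5.3). Section 5.4 allows the perfusion parameters to be completed in batch up to 6 months after radiosurgery, with the reason "Given the DSC-PMR data will not be used in clinical care".

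**The concern.** In an accuracy study the reference label should be set without the test being judged. Here the modality under study is a permitted input to the label of an unbiopsied lesion. Section 10.3 itself calls the separation of recurrence from necrosis difficult, and the two labels compete for the same enlarging lesion. If perfusion tips the clinical call towards necrosis, a primary-endpoint event disappears; if it tips the call towards recurrence, an event appears. Section 1.2 cites a study in which high CBV after SRS predicted recurrence, so a clinician could reasonably read a work-up scan that way.

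If a lesion's perfusion at Week 1 resembles its perfusion at work-up, Week 1 perfusion will partly predict a label that perfusion helped to set. The Cox association and the AUC could then look better than they are. Section 1.3 intends these data to lead to a phase II study of selective WBRT. A SAP could not repair this afterwards from the follow-up form, because the form does not show which labels relied on DSC-PMR.

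**Working it through.** **1. The plan's own figure.** 20 patients × 3 lesions = 60 lesions (section 10.1), which reproduces. At the 27–33% one-year recurrence cited in the Background, 60 × 0.27 = 16.2 and 60 × 0.33 = 19.8, so about 16 to 20 events. A few altered labels would matter.

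**2. Inputs the protocol does not give (all assumed).**
- e: share of lesions that enlarge, 0.40–0.50 (0.45 unless stated), unrelated to Week 1 perfusion, so the true AUC is 0.50.
- Half of the enlarging lesions are called recurrence.
- f: share of enlarging lesions whose label is set by later DSC-PMR. The other labels are unrelated to Week 1 perfusion.
- r: correlation of the predictor with later perfusion (normal variables, later value split at its median).

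**3. Formula.** With a = arcsin(r/√2)/π:
- AUC among enlarging lesions = 0.5 + 2fa
- AUC over all lesions = 0.5 + fa/(1 − e/2)

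**4. Absolute Week 1 value, r = 0.5.** a = arcsin(0.354)/π = 0.115 and 1 − e/2 = 0.775.

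| Labels set by later DSC-PMR | f | AUC, all lesions |
|---|---|---|
| Every enlarging lesion | 1 | 0.5 + 0.115/0.775 = 0.65 |
| All except 30% set by pathology | 0.70 | 0.5 + 0.70 × 0.148 = 0.60 |
| Half of the remaining 70% | 0.35 | 0.5 + 0.35 × 0.148 = 0.55 |

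With f = 1, the AUC among enlarging lesions is 0.5 + 2 × 0.115 = 0.73. Moving e from 0.40 to 0.50 changes 0.65 only between 0.64 and 0.65. Simulation agrees with these values. With r from 0.3 to 0.7, 50–70% called recurrence and f = 1, the simulated all-lesion AUC runs from 0.56 to 0.72.

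**5. Change from baseline, the primary predictor.** With equal variances, the change correlates with later perfusion at r_c = (r_week1 − r_base)/√(2(1 − r_bw)), where r_bw is the baseline–Week 1 correlation.
- If baseline and Week 1 correlate equally with later perfusion, r_c = 0 and the AUC is 0.50.
- If r_week1 = 0.5, r_base = 0.25 and r_bw = 0.5, then r_c = 0.25, a = 0.0566, and the AUC is 0.5 + 0.0566/0.775 = 0.57.
- With r_base = 0.35 instead, r_c = 0.15 and the AUC is 0.54.
- With f = 0.35, the 0.57 becomes 0.5 + 0.35 × 0.073 = 0.53.
- A higher r_bw raises the figure: at r_bw = 0.7 and r_base = 0.25, r_c = 0.32 and the AUC is about 0.60 with f = 1.

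**6. A second model, with a true disease state.** Assumptions: 30% recurrence, necrosis mimics in 5–20% of lesions, 30% of suspected lesions biopsied, and DSC-PMR deciding 50–100% of the rest. The work-up scan is given the 91% sensitivity and 71% specificity quoted in section 1.2 (from 6 weeks after SRS). The correlation is that between Week 1 and work-up readings, given true status.

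| Correlation | True AUC 0.50 | True AUC 0.70 |
|---|---|---|
| 0 | 0.50 | 0.67–0.69 |
| 0.6 | 0.52–0.56 | 0.71–0.73 |
| 0.9 | 0.53–0.60 | 0.72–0.77 |

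Upward bias therefore needs correlated readings. Without correlation, a null marker stays null and a real effect is slightly attenuated.

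**The case against.** A reader might infer that the outcome is made from the index test. The documents do not support that. The index test is the baseline-to-Week 1 change, whereas section 5.6 concerns a later scan that is optional, is listed beside serial MRI and PET, and follows a suspicion already raised on follow-up MRI. Unbiopsied recurrence is also governed by the MacDonald criteria; the wording about a final clinical diagnosis is the necrosis rule, and necrosis is a secondary endpoint. This objection stands as a limit on the claim. It does not close the path, because both labels apply to the same enlarging lesion and neither rule excludes perfusion findings.

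A reader might also infer that the AUC is certain to be inflated. Size and direction depend on a correlation the protocol does not give. The largest figures belong to the absolute Week 1 value with DSC-PMR deciding every enlarging lesion, which is close to a worst case.

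Third, a reader might see a plain contradiction between sections 5.3 and 5.4. They can be read together: the Week 1 report is explained by incidental findings (new metastases, bleeding, stroke), while section 5.4 may mean only the batch-processed research parameters. Nothing says those parameters enter the clinical record. The wording still leaves open whether DSC-PMR results inform care, as section 5.6 allows.

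Finally, excluding DSC-PMR from the label has a price. At 40–50% enlarging, 60 × 0.40 = 24 to 60 × 0.50 = 30 lesions could be affected before any biopsies if DSC-PMR decided them all. If it decides few, the cost and the bias are both small.

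**Conclusion.** The concern holds as a risk, not as a demonstrated bias. Followed as written, the protocol lets the modality under study contribute to the primary-endpoint label of unbiopsied lesions, and keeps no record on the follow-up form of where this happened.

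For a predictor with no real value and a correlation of 0.5 with later perfusion, the absolute Week 1 value could show an AUC of about 0.65 at the extreme. It would be about 0.55 if DSC-PMR decides half of the lesions and 30% of labels come from pathology. The change from baseline could show about 0.50–0.57, or about 0.60 if baseline and Week 1 values are themselves highly correlated. With uncorrelated readings there is no inflation. Every input on enlargement, correlation, biopsy and use of DSC-PMR is an assumption. The point should be addressed because a cheap safeguard exists and the result is meant to support a further trial.

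**What to change.** - **Section 10.3:** state that the study label comes from pathology or, without it, from structural MRI under the MacDonald criteria, PET and clinical course, and not from any DSC-PMR result.
- **Appendix B:** add a field for the basis of diagnosis of each lesion (pathology, structural MRI, PET, DSC-PMR).
- **Analysis:** add a sensitivity analysis that leaves out lesions whose clinical label relied on DSC-PMR.
- **Sections 5.3, 5.4 and 5.6:** reconcile what they say on whether DSC-PMR results enter clinical care.

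Treating physicians keep full discretion over work-up and diagnosis; only the label used in the analysis is governed. The cost is a few sentences and one form field, with no extra scan, reader or biopsy. The real downside is that some unbiopsied lesions, possibly more than a few, are labelled for the study with less information, which may add some misclassification between recurrence and necrosis.

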# STUDY CALENDAR

|  | **Baseline ^D^** | **Week 1** | **Follow-Up ^A^** |
| --- | --- | --- | --- |
| Physical exam, medical history, KPS | X |  | X |
| MRI w/contrast | X |  | X |
| Blood for plasma creatinine | X |  | X |
| GK | X |  |  |
| DSC-PMR | X ^C^ | X |  |
| Adverse event assessment | X ^B^ | X ^B^ |  |

A: Standard follow-up will be done at every 3 months after GK for at least one year as part of routine clinical practice. The research coordinator will audit the medical record to record outcomes as documented during routine follow-up.

B: Patients will be followed for adverse events for 8 hours following each research DSC-PMR scan. If the baseline scan is performed as part of the patient’s routine care, patients need not be monitored for AEs as that procedure is performed outside the scope of this protocol.

C: At least one baseline DSC-PMR must be done, either at screening or time of GK (or both).

D: Data will be collected from the indicated standard of care pre-treatment assessments, but these assessments are not dictated by the protocol.

# DATA SUBMISSION SCHEDULE

| **Case Report Form** | **Time point** |
| --- | --- |
| Consent Form | At time of consent |
| Eligibility Checklist  Registration  On-Study Form | At time of registration |
| GK Form | At time of GK |
| DSC-PMR Form | Baseline/screening or at time of GK (or both)  1 week after GK  [*The DSC-PMR parameters in Appendix C May be completed up to 6 months from the time of radiosurgery] |
| Adverse Events Form | AE information will be collected during the 8-hour period following each research DSC-PMR scan |
| Follow-Up Form | 3 months after GK  6 months after GK  9 months after GK  12 months after GK |

# REGULATORY AND REPORTING REQUIREMENTS

Since this is a diagnostic study that does not involve any experimental forms of cancer therapy, adverse event reporting is expected to be minimal. Any medical treatment needed for an adverse reaction to the MRI would be taken care of in the clinic or consultation room by the investigators or by the patient’s regular physician. If any adverse events occur, they will be graded according to CTCAE version 4.

Participants will be monitored for adverse events during the actual imaging period. Participants who experience an adverse event up to 8 hours post-scan will be instructed to inform the treating physician or principal investigator, who will then complete the appropriate reporting forms.

## Adverse Events (AEs)

Definition: any unfavorable medical occurrence in a human subject including any abnormal sign, symptom, or disease.

Grading: the descriptions and grading scales found in the revised NCI Common Terminology Criteria for Adverse Events (CTCAE) version 4.0 will be utilized for all toxicity reporting. A copy of the CTCAE version 4.0 can be downloaded from the CTEP website.

Attribution (relatedness), Expectedness, and Seriousness: the definitions for the terms listed that should be used are those provided by the Department of Health and Human Services’ Office for Human Research Protections (OHRP). A copy of this guidance can be found on OHRP’s website:

<http://www.hhs.gov/ohrp/policy/advevntguid.html>

## Unanticipated Problems

Definition:

- unexpected (in terms of nature, severity, or frequency) given (a) the research procedures that are described in the protocol-related documents, such as the IRB-approved research protocol and informed consent document; and (b) the characteristics of the subject population being studied;
- related or possibly related to participation in the research (in this guidance document, possibly related means there is a reasonable possibility that the incident, experience, or outcome may have been caused by the procedures involved in the research); and
- suggests that the research places subjects or others at a greater risk of harm (including physical, psychological, economic, or social harm) than was previously known or recognized.

## Noncompliance

Definition: failure to follow any applicable regulation or institutional policies that govern human subjects research or failure to follow the determinations of the IRB.  Noncompliance may occur due to lack of knowledge or due to deliberate choice to ignore regulations, institutional policies, or determinations of the IRB.

## Serious Noncompliance

Definition: noncompliance that materially increases risks, that results in substantial harm to subjects or others, or that materially compromises the rights or welfare of participants.

## Protocol Exceptions

Definition: A planned deviation from the approved protocol that are under the research team’s control. Exceptions apply only to a single participant or a singular situation.

Pre-approval of all protocol exceptions must be obtained prior to the event.

## Reporting to the Human Research Protection Office (HRPO) and the Quality Assurance and Safety Monitoring Committee (QASMC) at Washington University

The PI is required to promptly notify the IRB of the following events:

- Any unanticipated problems involving risks to participants or others which occur at WU, any BJH or SLCH institution, or that impacts participants or the conduct of the study.
- Noncompliance with federal regulations or the requirements or determinations of the IRB.
- Receipt of new information that may impact the willingness of participants to participate or continue participation in the research study.

These events must be reported to the IRB within **10 working days** of the occurrence of the event or notification to the PI of the event.  The death of a research participant that qualifies as a reportable event should be reported within **1 working day** of the occurrence of the event or notification to the PI of the event.

## Timeframe for Reporting Required Events

Reportable adverse events will be tracked for 8 hours following each research MRI.

| Deaths | |
| --- | --- |
| Any reportable death while on study or within 30 days of study | Immediately, within 24 hours, to PI and the IRB |
| Any reportable death while off study | Immediately, within 24 hours, to PI and the IRB |
| Adverse Events/Unanticipated Problems | |
| Any reportable adverse events as described in Sections 8.1 and 8.2 (other than death) | Immediately, within 24 hours to PI and within 10 working days to the IRB |
| All adverse events regardless of grade and attribution should be submitted cumulatively | Include in DSM report |
| Noncompliance and Serious Noncompliance | |
| All noncompliance and serious noncompliance as described in Sections 8.3 and 8.4 | Immediately, within 24 hours, to PI and within 10 working days to the IRB |

# DATA AND SAFETY MONITORING

In compliance with the Washington University Institutional Data and Safety Monitoring Plan, the Principal Investigator will provide a Data and Safety Monitoring (DSM) report to the Washington University Quality Assurance and Safety Monitoring Committee (QASMC) semi-annually beginning six months after accrual has opened (if at least five patients have been enrolled) or one year after accrual has opened (if fewer than five patients have been enrolled at the six-month mark). This report will include:

- HRPO protocol number, protocol title, Principal Investigator name, data coordinator name, regulatory coordinator name, and statistician
- Date of initial HRPO approval, date of most recent consent HRPO approval/revision, date of HRPO expiration, date of most recent QA audit, study status, and phase of study
- History of study including summary of substantive amendments; summary of accrual suspensions including start/stop dates and reason; and summary of protocol exceptions, error, or breach of confidentiality including start/stop dates and reason
- Study-wide target accrual and study-wide actual accrual
- Protocol activation date
- Average rate of accrual observed in year 1, year 2, and subsequent years
- Expected accrual end date
- Objectives of protocol with supporting data and list the number of participants who have met each objective
- Early stopping rules with supporting data and list the number of participants who have met the early stopping rules
- Summary of toxicities
- Abstract submissions/publications
- Summary of any recent literature that may affect the safety or ethics of the study

The study principal investigator and study coordinator will monitor for serious toxicities on an ongoing basis. Once the principal investigator or study coordinator becomes aware of a reportable adverse event (RAE), the RAE will be reported to the HRPO and QASM Committee according to institutional guidelines.

# STATISTICAL CONSIDERATIONS

## Sample Size

This is a nonrandomized imaging study with a pre-specified sample size of 20 patients. Different metastatic lesions treated with radiosurgery will be analyzed independently. Based on institutional experience, the average number of lesions is estimated at 3 per patient giving us a sample size of approximately 60 for the primary endpoint of local control.

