## Study Endpoint

The primary endpoint of the study is time to local progression of each treated and evaluable brain metastasis. Secondary endpoints will include radiation necrosis, complete response, elsewhere-brain failure, and clinical deterioration.

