## Statistical Tests

As it is not certain whether the absolute values of DSC-PMR parameters after treatment or the relative change of those parameters from the baseline scan would provide the best predictive value, we will analyze our DSC-PMR data using both methods. Time to local recurrence will be modeled using the Cox proportional hazard models. The Kaplan-Meier product-limit method will be used to estimate local control probabilities. Logistic repeated measures analysis of variance will be used to model the results of MR perfusion scans from baseline to Week 1 with respect to local progression. Receiver operating characteristic (ROC) curve and area under the ROC curve will be used to estimate the predictive accuracy of different DSC-PMR parameters in predicting local recurrence after GK.

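### About 60 lesions from 20 patients are counted and analysed as independent, with no allowance for lesions nested in patients

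*Protocol*

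**What the plan says.** Section 10.1 (Sample Size) fixes a "pre-specified sample size of 20 patients". It then states that "Different metastatic lesions treated with radiosurgery will be analyzed independently". On the basis that "the average number of lesions is estimated at 3 per patient", it arrives at the total, "giving us a sample size of approximately 60 for the primary endpoint of local control".

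Section 10.2 (Study Endpoint) makes the lesion the unit of the primary endpoint: "time to local progression of each treated and evaluable brain metastasis".

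Section 10.4 (Statistical Tests) names four methods:

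- Cox: "Time to local recurrence will be modeled using the Cox proportional hazard models".
- Kaplan-Meier, for local control probabilities.
- A repeated-measures model: "Logistic repeated measures analysis of variance will be used to model the results of MR perfusion scans from baseline to Week 1". The repetition here is over scans, not over lesions within a patient.
- ROC: "Receiver operating characteristic (ROC) curve and area under the ROC curve will be used to estimate the predictive accuracy".

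Nowhere does the protocol mention a frailty term, a cluster-robust variance, a patient random effect, resampling of patients, or a rule of one lesion per patient.

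**The concern.** Lesions in one patient are not separate experiments. They are imaged in the same session after the same contrast injection, and they would ordinarily share a primary cancer and systemic therapy. Local failure is therefore likely to be correlated within a patient, and perfusion values plausibly are too. An analysis that treats the lesions as independent then credits the data with more information than 20 patients supply.

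The primary aim is to find out how well perfusion changes predict local control. Section 1.3 (Significance) expects the data to support a phase II study that adds whole brain radiation selectively after radiosurgery. At the 27-33% one-year local recurrence quoted in the Background, 60 lesions give 60 × 0.27 = 16.2 to 60 × 0.33 = 19.8 events, and these may fall in few patients. Lesion counts may also be uneven: eligibility requires only one metastasis of at least 1 cm, while the forms in Appendices B and C have 15 rows. A few multi-lesion patients could drive an apparently precise result.

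**Working it through.** **Inputs from the protocol.** 20 patients and a mean of 3 lesions each (Section 10.1); one-year local recurrence of 27-33% after radiosurgery alone (Background). No intra-patient correlation (ICC), alpha, power or effect size is given, so every ICC below is an assumption shown over a range.

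**Step 1. The plan's own figure.** 20 × 3 = 60. It reproduces exactly, so 60 is a raw lesion count with no deduction for clustering.

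**Step 2. Kaplan-Meier local control.** For an average over lesions with m = 3 per patient, the design effect is DE = 1 + (m − 1) × ICC, and the effective number is 60/DE. The unadjusted standard error is too small by the factor √DE.

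| Assumed ICC | DE | Effective lesions | √DE |
|---|---|---|---|
| 0.1 | 1.2 | 50 | 1.10 |
| 0.3 | 1.6 | 37.5 | 1.26 |
| 0.5 | 2.0 | 30 | 1.41 |

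Uneven lesion counts make this worse. As an illustration only, let the count be 1 + Poisson(2): mean 3, SD √2, so CV = 1.414/3 = 0.47. Then DE = 1 + ((CV² + 1) × 3 − 1) × ICC = 1 + 2.67 × ICC. This gives 1.27 at ICC 0.1 (about 47 lesions) and 2.33 at ICC 0.5 (about 26).

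**Step 3. A lesion-level predictor (Cox hazard ratio, AUC).** Both the predictor (ICC_x) and the outcome (ICC_y) must be correlated within patient: DE ≈ 1 + (m − 1) × ICC_x × ICC_y. The actual size of a nominal two-sided 5% test is about 2 × (1 − Φ(1.96/√DE)).

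| ICC_x / ICC_y | DE | Actual size |
|---|---|---|
| 0 / any | 1.00 | 5.0% |
| 0.1 / 0.1 | 1.02 | 5.2% |
| 0.3 / 0.3 | 1.18 | 7.1% |
| 0.5 / 0.5 | 1.50 | 11.0% |
| 0.8 / 0.5 | 1.80 | 14.4% |

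**Step 4. Check by simulation.** The setting was 20 patients × 3 lesions, 30% one-year recurrence, no true effect of the predictor, a shared gamma frailty, follow-up to 12 months and 2,000 runs per setting. The table shows rejection by the unadjusted Cox test at nominal 5%.

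| Frailty variance | ICC_x = 0 | 0.3 | 0.6 | 0.9 |
|---|---|---|---|---|
| 0 | 4.1% | 4.9% | 4.8% | 4.7% |
| 1 | 5.8% | 6.7% | 8.8% | 11.6% |
| 2 | 5.2% | 7.8% | 10.8% | 12.8% |
| 4 | 5.7% | 10.1% | 14.6% | 18.4% |

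The unadjusted AUC test behaved similarly: 3.7% to 5.1% with no frailty, and up to 16.8% at the bottom right. With counts of 1 + Poisson(2) the Cox pattern was the same. The column with an uncorrelated predictor then ran from 4.7% to 7.0%, and the highest value was 21.0%. The simulation agrees with the formula: inflation needs correlation on both sides, and it is large only when both are strong.

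**The case against.** The best defence is that analysing lesions independently may mean only that the lesion is the unit, as Section 10.2 says, and that the variance estimator can be left to a statistical analysis plan that is not shown. The second half would carry weight if the protocol were silent. It is not: the independence statement is followed at once by a count of 60 offered as the sample size. A later plan that adjusted for patient would depart from this text, and one that followed it would carry the assumption forward.

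Other objections stand, and they limit the point. A reader might infer any of the following, and the documents do not support them:

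- *Every primary analysis has an inflated false-positive rate.* Size stays near 5% for the Cox and AUC tests if either correlation is absent, and the protocol reports neither. It also states no alpha or decision rule. Kaplan-Meier and AUC are described as estimation, so for them the harm is intervals that are too narrow.
- *Sharing a death or follow-up time is enough.* That is common censoring, not correlated failure. A simulation with shared death and no frailty gave a Cox size of 4.9% at predictor ICC 0.3 and again at 0.9.
- *The lesions share reference tissue.* Section 5.4 describes a contralateral region matched to the region of interest, which does not show that one region serves all lesions. Relative values and changes from baseline may also remove part of the common session effect.
- *The loss to 50 or 30 lesions applies to the hazard ratio.* It applies to the local control estimate. At 0.3/0.3 the predictor analysis keeps 60/1.18, about 51 lesions.
- *A power claim collapses.* None is made, and the 20 patients are pre-specified, not derived from the 60. Point estimates are not the main problem either.

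**Conclusion.** The point holds in a limited and conditional form. The protocol states an independence rule, uses it to present 60 as the sample size, and names no method that recognises the patient as a cluster. Given that lesions in one patient are likely to be correlated, 60 overstates the information and unadjusted intervals are likely to be too narrow.

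The size rests on assumed correlations. With 3 lesions each and ICC 0.1 to 0.5, Kaplan-Meier local control has the precision of about 50 down to 30 independent lesions. For a lesion-level perfusion predictor, 0.1/0.1 to 0.5/0.5 implies a design effect of about 1.02 to 1.5 and an actual size of about 5% to 11% for a nominal 5% test. Higher values arise only under stronger correlation. The correction is worth making because it bears on the primary aim and costs little.

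**What to change.** - **Section 10.1.** Replace the independence sentence with: the lesion is the unit of analysis and the patient is the cluster. Describe the sample as 20 patients contributing about 60 correlated lesions. Effective numbers over a range of ICCs, as in the working, could be added.
- **Section 10.4.** State that each analysis accounts for clustering by patient, using methods suited to about 20 clusters. Several are acceptable. For the Cox model: a leave-one-patient-out jackknife, a robust variance with a small-sample correction, or a shared frailty. For the logistic model: GEE or a patient random effect. For local control and AUC: intervals from a bootstrap that resamples patients.

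The small-sample correction matters. In a simulation of 20 patients with 1 + Poisson(2) lesions and frailty variance 0.5 to 2, an uncorrected clustered sandwich variance still rejected in 7.8% to 11.4% of null runs. A patient-level jackknife with a t reference on 19 degrees of freedom rejected in 3.4% to 4.8%. The jackknife is one valid choice, not the only one.

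The cost is wording in two sections, a little more analysis work and wider reported intervals. No extra patients or procedures are needed.
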